# Hemoperfusion with HA380 in acute type A aortic dissection patients undergoing aortic arch operation (HPAO): a randomized, controlled, double-blind clinical trial

**DOI:** 10.1186/s13063-020-04858-2

**Published:** 2020-11-23

**Keywords:** HA380, Acute type A aortic dissection, Cardiopulmonary bypass, Deep hypothermic circulatory arrest, Inflammatory factors, Coagulation indicators

## Abstract

**Background:**

Cardiopulmonary bypass (CPB) is an important cause of significant systemic inflammatory response syndrome (SIRS) in the surgical treatment of acute type A aortic dissection (ATAAD). In patients with arch vessel involvement, extensive surgical repairs often necessitate prolonged use of CPB and results in extensive inflammatory responses. Cytokines and chemokines released during CPB contribute to the progression of SIRS, increase perioperative complications, and negatively impact surgical outcomes. A cytokine adsorber (HA380) is expected to reduce the level of cytokines during CPB, which may decrease both intraoperative and postoperative inflammation. The purpose of this study is to investigate if HA380 is able to reduce the levels of inflammatory cytokines and decrease perioperative complications in ATAAD patients undergoing CPB and deep hypothermic circulatory arrest (DHCA).

**Methods:**

This study is a single-center, randomized, controlled, double-blind clinical trial. The study aims to recruit 88 patients with ATAAD and aortic arch involvement who will undergo CPB and DHCA to repair the dissected aorta. Patients will be randomized equally into the CPB/DHCA only group (control group) and the CPB/DHCA + HA380 hemoperfusion group (intervention group), with 44 patients each. Patients in the control group will undergo CPB and DHCA only, while patients in the intervention group will undergo continuous hemoperfusion with HA380, in addition to CPB and DHCA. The primary outcome is a composite of major perioperative complications. The secondary outcomes include related inflammatory markers, coagulation parameters, and minor perioperative complications. To comprehensively evaluate the effect of hemoperfusion on the perioperative outcomes, we will also determine if there are differences in perioperative all-cause mortality, length of ICU stay, and total hospitalization costs.

**Discussion:**

In the current trial, hemoperfusion will be applied in patients undergoing CPB and DHCA for repair of the aorta involving the aortic arch. This trial aims to test the safety and efficacy of our hemoperfusion device (HA380) in such settings. Upon completion of the trial, we will determine if HA380 is effective in reducing perioperative proinflammatory cytokine levels. Further, we will also verify if reduction in the proinflammatory cytokine levels, if present, translates to improvement in patient outcomes.

**Trial registration:**

ClinicalTrials.gov NCT04007484. Registered on 1 July 2019 (retrospectively registered).

## Background

Cardiovascular disease is the leading cause of death worldwide [1]. In the last couple of decades, the advancement of cardiac surgery has enabled invasive management and improved overall outcomes in patients with heart and great vessel diseases. Cardiopulmonary bypass (CPB) is an indispensable technique used in open-heart surgery that ensures perfusion of vital organs with a stopped heart. While essential, CPB can induce the massive release of inflammatory cytokines, causing overwhelmed systemic inflammation reactions that may increase perioperative mortality.

It is estimated that the incidence of systemic inflammatory response syndrome (SIRS) in patients undergoing CPB can reach as high as 40% to 50% [2, 3]. During CPB, contact of blood with artificial materials activates monocytes and macrophages, both of which release inflammatory cytokines and induce inflammation [4]. In patients who developed SIRS after CPB, white blood cell count and multiple inflammatory markers such as interleukin (IL)-6, IL-8, and tumor necrosis factor-α (TNF-α) were all significantly increased [5–7]. In addition, the severity of SIRS, marked by inflammatory cytokines, after cardiac surgery directly correlates to the perioperative complications and prognosis [8–10].

Acute type A aortic dissection (ATAAD) is a cardiovascular emergency that requires immediate open surgical treatment. In the surgical treatment of ATAAD, the extensive repair necessitates prolonged use of CPB, which exacerbates inflammation and negatively impact surgical outcomes. Because the levels of inflammatory markers influence the severity of SIRS and prognosis, measures to reduce inflammation have always been the center of focus in open-heart surgery.

Hemoperfusion is a technique widely used in toxicology for the removal of toxins. It works by removing cytokines that cannot be filtered using existing blood purification techniques [11]. Recent studies suggested that hemoperfusion is also able to absorb inflammatory mediators produced during CPB and produce a long-lasting anti-inflammatory effect [12]. However, the role of hemoperfusion in the settings of ATAAD patients undergoing CPB and deep hypothermic circulatory arrest (DHCA) is currently unknown. In the present study, we would like to determine if hemoperfusion is able to reduce inflammatory mediators and reduce the perioperative complications in ATAAD patients undergoing CPB and DHCA.

### Objective and hypothesis

This study is a single-center, randomized, controlled, double-blind clinical trial. Subjects undergoing DHCA/CPB will be allocated to the hemoperfusion group and control group. The main purpose of this study is to determine if the levels of pro-inflammatory cytokines and anti-inflammatory cytokines differ between the two study groups in the perioperative period. In addition, differences in perioperative coagulation parameters, blood product usages in the intensive care unit (ICU), length of hospital stay, postoperative complications, and all-cause mortality between two groups will also be determined. We hypothesize that hemoperfusion could improve the overall prognosis in patients with acute type A aortic dissection undergoing cardiopulmonary bypass and DHCA.

## Methods

### Ethics and registration

This prospective, randomized, double-blind controlled study started recruiting patients at the Cardiovascular Center of the Second Affiliated Hospital of Nanjing Medical University in China in January 2019 and is expected to complete within 24 months (30 December 2020). The design of the trial follows the guidelines in the Helsinki Declaration and is in accordance with the guidelines of the Medical Research Involving Human Subjects Act and Good Clinical Practice (GCP). This trial has been approved by the Ethics Committee of the Second Affiliated Hospital of Nanjing Medical University (No.[2018] KY 118) and has been registered at ClinicalTrials.gov (NCT 04007484). According to the Consolidated Standards of Reporting Trials (CONSORT) statement, the study flow chart is developed, as shown in Fig. 1.

**Fig. 1 Fig1:**
[figure not shown]
Flow chart of the hemoperfusion in acute type A aortic dissection patients undergoing aortic arch operation (HPAO) trial

### Patient and public involvement

Patients or the public are not involved in the design, conduct, reporting, or dissemination plans of our research.

### Research objects

#### Inclusion criteria

Patients aged 18–75 years, regardless of genderPatients with acute type A aortic dissection and arch involvement (onset time ≤ 7 days)Able to understand and sign the informed consent

#### Exclusion criteria

Unable to understand and sign the informed consentBMI ≥ 40PregnantActive hemorrhage or thrombocytopenic purpuraPrevious history of liver diseases, renal insufficiency, or cerebrovascular diseasesProlonged operation time due to intraoperative accidentPreoperative organ malperfusionPrevious history of cardiac surgeriesOral anticoagulant or antiplatelet drugs within 1 week of disease onsetHereditary connective tissue diseases such as Marfan syndrome, Ehlers-Danlos, and Loeys-Dietz syndrome

The listed exclusion criteria are set to minimize the impact of perioperative variables, which may potentially undermine the validity of the study. The exclusion criteria are also backed up by a number of studies focusing on cardiac surgery [13–15].

### Experimental intervention/treatment

Hemoperfusion is achieved through blood filtration with a hemoperfusion device named HA380 (Zhuhai Jafron Biomedical, China). The hemoperfusion device, composed of multiple parallel macroporous adsorption resin cartridges, is connected in parallel to the oxygenator and blood reservoir and perfused at a rate of 400–700 ml/min (Fig. 2). Thanks to the large medium and macroporous structure and high specific surface area, HA380 is able to adsorb superfluous inflammatory factors and excess metabolites in the blood through different forces. The outbreak of inflammatory factors is thus expected to be controlled. The aim of hemoperfusion is to decrease inflammatory mediators produced during cardiopulmonary bypass through adsorption. The ultimate goal of hemoperfusion is to decrease postoperative complications, improve postoperative recovery, and shorten the length of hospital stay. Montin et al. detailed the safety and effectiveness of HA380. General recommendations of HA380 in cardiac surgery have also been made [16].

**Fig. 2 Fig2:**
[figure not shown]
HA380 hemoperfutor setup in the CPB circuit. Venous blood first enters the venous reservoir, where it subsequently flows into the oxygenator with a driving force from a roller pump. After oxygenation, the majority of the oxygenated blood goes into the arterial circulation for perfusion, roughly 700 ml/min (14–18%) goes through the hemoperfusion device HA380 for hemofiltration. The filtered blood then returns to the venous reservoir and mixes with the venous blood. No other additional equipment is required

### Randomization and blinding

On the day of surgery, the perfusionists will explain to the patient’s families the context and significance of our trials and obtain informed consents. All informed consents will be kept in a separate folder and preserved by the project leader. Upon anesthesia, a statistician who does not participate in the experiments will use a computer software to randomly designate a number of either 0 or 1 to the patient, with 0 for the control group and 1 for the intervention group. The expected number of patients in the control group will equal that of the intervention group. To keep the trial confidential, the results of random allocation will only be known to the statisticians and perfusionists. Other physicians including cardiac surgeons, anesthesiologists, intensivists, and other clinicians will be blinded to the grouping. The details of randomization will not be accessible to anyone but the statisticians and perfusionists until the end of the trial and completion of the data analysis. If exclusion criteria are met after randomization (e.g., hemi-arch replacement is performed or deep hypothermia circulatory arrest not required), the patient will be removed from the trial.

During the hospital stay, only the perfusionists are aware of the grouping of patients. First of all, the size of HA380 is small. It is often not noticeable to the surgical team. Secondly, the shape of the device is no different to conventional filters used in CPB. Therefore, it is difficult to tell if HA380 is used just by eyeballing on the CPB circuit. Third, our HA380 are specially ordered and no label is visible on the device. Thus, only the perfusionist knows if the device was used. Cardiac surgeons, intensivists, and other clinicians actively involved in the treatment of the patients are blinded to patient grouping. The detail of randomization will not be revealed until the end of the study and completion of data analysis.

### Data collection using case report form (CRF)

Preoperative data including preoperative demographics (sex, age, BMI), details of presentation (onset time, symptoms such as chest pain, back pain, dyspnea, abdominal pain/abdominal distension, nausea/vomiting, coma, etc.), prior medical history (hypertension, hyperlipidemia, diabetes, coronary heart disease, kidney disease, cerebrovascular disease, smoking history, drinking history, etc.), preoperative imaging and laboratory results (such as electrocardiogram, cardiac ultrasound, computed tomography angiography, coagulation routine, liver and kidney functions, blood routine, etc.), and preoperative medications (norepinephrine, dopamine, urapidil, epinephrine, etc.) will be collected.

Intraoperative data including surgical methods, CPB details (CPB time, aortic cross-clamp time, circulatory arrest time, unilateral cerebral perfusion time, nasopharyngeal minimum temperature, etc.), volume of intraoperative blood products (such as suspended red blood cells, fresh frozen plasma, platelet, cryoprecipitate, etc.), amount of blood loss, and urine output will also be collected.

Postoperative follow-up data including major postoperative complications (new renal failure-requiring dialysis, secondary thoracotomy, operative mortality, stroke/cerebrovascular accident, paraplegia, acute renal injury, respiratory failure, delirium, severe liver dysfunction, myocardial infarction, etc.), general condition after operation (duration of mechanical ventilation, drainage volume within 24 h postoperatively, urine volume within 24 h postoperatively, the length of ICU stay, all-cause mortality, dosage of vasoactive drugs, total hospitalization cost, etc.), and volume of postoperative blood product transfusions will be collected. Utilization of invasive postoperative treatment methods such as continuous renal replacement therapy (CRRT) or extracorporeal membrane oxygenation (ECMO) will be documented as well. In general, all patients enrolled will be followed up at our center. Part of the data to be collected throughout the study is shown in Fig. 3.

**Fig. 3 Fig3:**
[figure not shown]
Schedule of enrollment, intervention, perioperative data, and laboratory parameters at different time points on the basis of Standard Protocol Items: Recommendations for Interventional Trials (SPIRIT) Statement. T0, before operation; T1, CPB initiation; T2, lowest intraoperative temperature; T3, end of CPB; T4, end of the operation; T5, 24 h after completion of the procedure; T6, 48 h after completion of the procedure; T7, 72 h after completion of the procedure; CPB, cardiopulmonary bypass; DHCA, deep hypothermic circulatory arrest; CRRT, continuous renal replacement therapy; ECMO, extracorporeal membrane oxygenation; MIF, macrophage migration inhibitory factor; PO 3M, postoperative 3 months; PO 6M, postoperative 6 months

It should be noted that contrast-enhanced thoracic computed tomography aortography (CTA) needs to be provided before operation to confirm the diagnosis, and the data of preoperative examinations is the closest one to the operation. Preoperative and postoperative data will be collected and recorded by team members who are blinded to surgical details and randomization. Intraoperative data will be collected by perfusionists and anesthesiologists.

### Anesthesia and surgical procedures

Venous access is achieved through peripheral vein puncture in the operating room. Throughout the surgery, five-lead electrocardiogram (ECG), blood oxygen saturation (SPO_2_), and heart rate (HR) should be routinely monitored with patient monitor (Philips, Holland). Non-invasive cerebral oxygen saturation (rSO_2_) and BIS monitoring are achieved with Disposable sensor (Covidien, USA). During the operation, the value of rSO_2_ is maintained at no less than 80% of baseline with an absolute value greater than 50%. Induction of anesthesia is achieved with etomidate 10 to 15 mg, sufentanil 0.5–1 μg/kg, and cis-atracurium 0.15 mg/kg intravenously. Anesthesia is maintained with dexmedetomidine 0.2–0.4 μg/kg/h, sufentanil 1–3 μg/kg/h, cis-atracurium 0.06–0.12 mg/kg/h, and sevoflurane, at a BIS between 40 and 60.

After median thoracotomy, the supra-aortic branches are isolated. Once ACT reaches 480 s, cardiopulmonary bypass is started. Throughout the CPB, the flow rate is kept at 2 to 2.5 l/min/m^2^, and the mean arterial pressure is maintained between 50 and 70 mmHg (1 mmHg = 0.133 kPa). Cooling down of the patient is subsequently initiated while ascending aorta is being opened and false lumen thrombus being removed. Subsequently, the dissected proximal aorta is replaced with or without replacement of the prosthetic aortic valve while the patient is being cooled down. To minimize cerebral ischemia, arch vessels are reconstructed with the following sequence respectively: the left carotid artery, the left subclavian artery, and the right innominate artery. After completion of repair and rewarming, the patient is weaned from CPB. Protamine is given to reverse the effect of heparin if needed. The procedure completes after hemostasis is reached and the sternum is closed.

### Blood sample collection and detection

During the perioperative period, plasma inflammatory factors levels will be measured at the following time points: before operation (T0), CPB initiation (T1), lowest intraoperative temperature (T2), end of CPB (T3), end of the operation (T4), 24 h after completion of the procedure (T5), 48 h after completion of the procedure (T6), and 72 h after completion of the procedure (T7).

Parameters of coagulation including plasma-activated partial thromboplastin time (APTT), prothrombin time (PT), fibrinogen (FIB), fibrinogen degradation product (FDP), and d-dimer (DDi) levels will be measured at the following time points: before operation, 24 h after completion of the procedure (POD 1), 48 h after completion of the procedure (POD 2), and 72 h after completion of the procedure (POD 3).

Similarly, levels of coagulation factors including II, VII, IX, X, XI, and XII will be measured at the following time points: before operation, end of CPB, end of the operation, 24 h after completion of the procedure (POD 1), and 48 h after completion of the procedure (POD 2).

Measurement of inflammatory cytokines levels: blood samples are collected through radial artery catheterization. The first 5 ml will be discarded when sampling. Following collection, blood samples are immediately centrifuged at 3000 rpm for 15 min at 4 °C. The plasma yielded will be stored in the − 80 °C refrigerator till the time of measurements. Enzyme-linked immunosorbent assay (ELISA) is used for the measurement of inflammatory cytokines.

### Primary outcome measures

Incidence of composite major complications [time frame: up to 30 days]:
Operative mortalitySecondary thoracotomyNew onset of postoperative renal failure requiring dialysis: increase in serum creatinine value ≥ 300% from baseline or an absolute serum creatinine ≥ 354 μmol/l with an increase ≥ 44 μmol/l from baseline (KDIGO stage 3) [17]. Any patient who received acute dialysis is put into this category. Patients who have received dialysis within 1 month prior to the surgery are not eligible for this endpointParaplegiaStroke/cerebrovascular accidentsLow cardiac output syndrome: cardiac index < 2.0 l min^−1^ m^−2^ for > 8 h after surgery, regardless of treatment [18]ReintubationSevere liver dysfunction: ALT level above 500 U/l or a total bilirubin above 3.0 mg/dl [19, 20]ECMO supportMultiple organ dysfunction syndrome (MODS)

Each of these outcomes will be analyzed as a secondary endpoint.

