### Secondary outcome measures

Changes in the levels of plasma inflammatory factors such as IL-6, IL-8, IL-10, IL-1β, and TNF-α [time frame: up to 3 days]Changes of plasma MIF levels during the perioperative period [time frame: up to 3 days]Changes of plasma CRP levels during the perioperative period [time frame: up to 3 days]Changes of the plasma II, VII, IX, X, XI, and XII levels during the perioperative period [time frame: 2 days]Changes of the plasma APTT, PT, FIB, FDP, and DDi levels during the perioperative period [time frame: 3 days]Total drainage within the first 24 h of surgery [time frame: 24 h]Incidence of postoperative acute kidney injury [time frame: up to 30 days]: increase in serum creatinine ≥ 150% or ≥ 26.5 μmol/l from baseline [13]Incidence of postoperative respiratory failure [time frame: up to 30 days]: uninterrupted postoperative mechanical ventilation for more than 48 h [10]Incidence of postoperative delirium [time frame: up to 30 days]: we will assess delirium once a day for a total of 3 times during the first 72 h after ICU admission, using standard delirium assessments (CAM or CAM-ICU). Before the CAM-ICU will be performed, a Richmond Agitation Sedation Scale (RASS) sore should be evaluated in advance [21]Incidence of postoperative liver injury [time frame: up to 30 days]: ALT level above 150 U/l [22]Incidence of postoperative myocardial infarction [time frame: up to 30 days]: a rise and/or fall of cTn values with at least 1 value above the 99th percentile upper reference limit and at least 1 of the following:
Symptoms of myocardial ischemiaNew ischemic ECG changesDevelopment of pathological Q wavesImaging evidence of new loss of viable myocardium or new regional wall motion abnormality in a pattern consistent with an ischemic etiologyIdentification of a coronary thrombus by angiography or autopsy (not for types 2 or 3 MIs) [23]

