### Sample size calculation

Primarily, we expect the incidence of composite major complications to be decreased in the HA380 hemoperfusion group (intervention group) compared with the control group. The sample size was calculated with our preliminary results from the pilot study, in which the primary outcome was defined as the incidence of composite major complications. In this study, we included 24 patients (*n* = 12 in each group), in which 8.3% (1 out of 12) of the patients assigned to the intervention group underwent CRRT due to severe postoperative renal failure. In contrast, 33.3% (4 out of 12) patients had either one of the following outcomes: death, secondary thoracotomy, and renal failure requiring dialysis. Assuming a two-sided type I error probability (α) of 5% and type II error probability (β) of 20%, forty patients are needed in each group. Suppose 10% of patients drop out either due to changes in surgical methods or lost in follow-up, a minimum number of 44 patients in each group are needed in order to achieve statistical significance.

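### Both liver outcomes use absolute cut-offs with no reference to the preoperative value, so an abnormality that was present before surgery and persists after it is scored as an event

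*Protocol article*

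**What the plan says.** In the protocol article, Primary outcome measures, one of the ten composite components is severe liver dysfunction: "ALT level above 500 U/l or a total bilirubin above 3.0 mg/dl". The composite is scored as "Incidence of composite major complications [time frame: up to 30 days" from surgery. Under Secondary outcome measures the milder liver outcome reads "Incidence of postoperative liver injury [time frame: up to 30 days]: ALT level above 150 U/l". Neither carries a baseline term, a new-onset condition or a rule for patients already above the limit.

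The kidney outcomes in the same two lists are built differently. The primary renal component is labelled as new onset and, unless acute dialysis is given, needs an "increase in serum creatinine value ≥ 300% from baseline or an absolute serum creatinine ≥ 354 μmol/l with an increase ≥ 44 μmol/l from baseline". Patients dialysed in the month before surgery cannot score it. Secondary acute kidney injury is an "increase in serum creatinine ≥ 150% or ≥ 26.5 μmol/l from baseline".

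Exclusion criteria remove patients with a history of liver disease and patients with preoperative organ malperfusion, but set no limit on ALT or bilirubin. Preoperative laboratory data are recorded, including "coagulation routine, liver and kidney functions, blood routine, etc" (Data collection using case report form), and the text accompanying Fig. 3 says that the examination nearest to the operation is the one used.

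**The concern.** With an absolute cut-off alone, the outcome records the state of the liver at some time after surgery, not a change that surgery or the device could have caused. Enrolment is allowed up to 7 days after onset, and a patient can arrive with a raised ALT or bilirubin without known liver disease or recognised malperfusion. An ALT of 180 U/l that falls to 160 U/l is then scored as postoperative liver injury. A bilirubin of 3.2 mg/dl that stays at 3.2 mg/dl is scored in the primary composite.

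Such events cannot be prevented by HA380. They add the same expected number to each arm, pull the risk ratio toward 1 and cost power. With 44 patients per arm, a few of them could also fall unevenly by chance.

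The plan's own treatment of the kidney makes the gap visible. A history of renal insufficiency is excluded in the same line as liver disease, yet the renal outcomes still refer to baseline. For the kidney, then, the history exclusion does not stand alone; for the liver outcomes the definitions add nothing to the exclusions.

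**Working it through.** **1. Definitions side by side.**

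| Outcome | Refers to preoperative value? | Rule for patients already affected? |
|---|---|---|
| Renal failure (primary) | Yes, except that acute dialysis counts by itself | Yes, recent dialysis cannot score |
| Acute kidney injury (secondary) | Yes | Not needed, since a rise is required |
| Severe liver dysfunction (primary) | No | No |
| Liver injury (secondary) | No | No |

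**2. The plan's own sample size.** Inputs from Sample size calculation: intervention "8.3% (1 out of 12) of the patients assigned to the intervention group underwent CRRT", so p2 = 1/12; comparison arm "33.3% (4 out of 12) patients had either one of the following outcomes: death, secondary thoracotomy, and renal failure requiring dialysis", so p1 = 1/3; two-sided α = 0.05; power 80%; 1:1 allocation. The pooled-variance formula without continuity correction is

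n = [1.96·√(2·p̄(1−p̄)) + 0.842·√(p1(1−p1) + p2(1−p2))]² / (p1−p2)²

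With p̄ = 0.2083, the two roots are 0.574 and 0.546, so n = (1.126 + 0.460)² / 0.0625 ≈ 40.2, or 41 rounded up. The stated 40 is reproduced to within one patient, and 40 × 1.10 = 44. This point does not dispute that figure.

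**3. Dilution of the composite.** Let q be the share of patients in each arm who score through a carried-over liver abnormality. Assume that this is independent of the other components and of treatment. The documents give no q, so the values below are assumptions.

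Observed rate = 1 − (1−p)(1−q), so the risk difference shrinks by the factor (1−q).

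Power = Φ{[d·√n − 1.96·√(2·p̄(1−p̄))] / √(p1(1−p1) + p2(1−p2))}, where d is the observed risk difference and p1, p2 and p̄ are now the observed rates.

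| q (assumed) | Control | HA380 | Risk difference | Risk ratio | Power, 40/arm | Power, 44/arm |
|---|---|---|---|---|---|---|
| 0 | 33.3% | 8.3% | 25.0 points | 0.25 | 79.8% | 83.5% |
| 2% | 34.7% | 10.2% | 24.5 points | 0.29 | 75.7% | 79.7% |
| 5% | 36.7% | 12.9% | 23.75 points | 0.35 | 69.8% | 74.0% |

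Check of the 2% row at n = 40: d·√40 = 0.245 × 6.325 = 1.550; 1.96 × 0.590 = 1.156; (1.550 − 1.156) / 0.564 = 0.698; Φ(0.698) = 0.757.

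In patients, 2% of 88 is 1.76 and 5% is 4.4 across both arms.

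**4. Why these are upper bounds.** If q is taken as the share above the cut-off at entry, the carried-over share cannot exceed it, because a value must still be above the cut-off after surgery and some will have fallen.

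**5. The secondary outcome.** The lower threshold lets in more patients. Taking, purely for illustration, true rates of 20% v 10% and q = 10%: 1 − 0.80 × 0.90 = 28% and 1 − 0.90 × 0.90 = 19%. The risk ratio is 0.19/0.28 = 0.68 instead of 0.50. All three inputs are assumed.

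**The case against.** The case for leaving the definitions alone has several parts.

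- **Eligibility.** A reader might infer that only a liver history is barred. That is wrong: preoperative organ malperfusion is also excluded, and this should remove some patients with ischaemic liver injury, chiefly those with ALT above 500 U/l. This stands as a limit on size. The exclusion is stated without a laboratory criterion, so it does not settle the matter.
- **Timing.** A reader might infer that a patient with raised bilirubin has the primary event before the device is connected. The documents do not support that. The case report form section lists severe liver dysfunction among postoperative complications, and the composite is an incidence over 30 days, so a preoperative value alone is not an event. This stands. But the wording fixes when the value is read, not that it must be new, and a persisting abnormality still counts.
- **Bias.** Randomisation balances such patients in expectation. There is no systematic advantage to either arm and no inflation of type I error. Components are also analysed singly, so a composite result driven by liver events would be visible. This stands; what remains is dilution and possible chance imbalance.
- **Size.** No prevalence is given, and the pilot events behind 33.3% and 8.3% mention no liver event. This stands, and the figures above show only what an assumed share would do.
- **Condensed article.** A rule for values abnormal at entry might sit in the full protocol or in the cited sources. But the article states explicit definitions for both liver outcomes and gives baseline rules for the kidney, so this is a criterion as fixed, not a detail left out.

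**Conclusion.** The point holds in a limited form. As written, both liver outcomes count an abnormality that preceded surgery and persisted, one of them inside the primary composite, while the kidney outcomes in the same lists guard against this. The consequence is non-differential dilution plus some room for chance imbalance, not bias in favour of HA380.

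The size cannot be fixed from the document. Under assumed carry-over of 2% to 5%, independent of the other components, power at 40 per arm would fall from about 80% to between 76% and 70%. These are upper bounds if the shares are read as entry prevalence. With both exclusions in force and the high primary cut-offs, the true effect on the primary outcome is probably small. The ALT above 150 U/l outcome is more exposed. This is a cheap improvement, not a threat to the trial's validity.

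**What to change.** Define both liver outcomes as new onset. Count the event only if the last preoperative value was at or below the same cut-off (for the primary component, both the ALT and the bilirubin cut-off). Treat a patient already above it as unable to score that liver component, as the plan does for recent dialysis. Keep that patient in the composite denominator, where every other component can still count. No patient is removed from the trial and eligibility is unchanged.

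For the sensitivity analysis, report both outcomes under the published definition, and state how many patients per arm were above each cut-off before surgery.

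The change costs one sentence in each definition and uses laboratory values already on the case report form. It has three drawbacks. Slightly fewer liver events will be counted. A true worsening in the few patients abnormal at entry will not count in that component. And the article appeared on 23 November 2020 with recruitment due to end on 30 December 2020, so a component of the primary outcome would be amended late. The amendment should therefore be dated, made before unblinding, and decided by team members without access to the allocation, which the statisticians and perfusionists hold.
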